### 4.3 Justification for Dose

In Part 1, the Phase 1 component of this protocol, 3 dose levels will be evaluated in a sequential manner, starting with the lowest dose. The dose determination is based on a combination of PK simulations to predict the PK profile of XVR011 in humans and a dose response model based on the antiviral efficacy of XVR011 in the hamster viral infection model. The simulated human PK profiles are based on PK data from a cynomolgus PK study of a single IV administration of 2 dose levels of XVR011 (5 mg/kg and 50 mg/kg). The hamster studies evaluated various doses, two viral isolates, therapeutic and prophylactic settings as well as RNA and infectious viral particle endpoints and lung histopathology. They correlate the *in vivo* efficacy with serum concentrations and allow for various sources of variability. The data from the hamster viral infection studies show a binary response, i.e. responder or non-responder when using a desired viral load decrease relative to plasma concentrations of XVR011. Fitting a logistic regression function to these data allow a threshold concentration to be determined corresponding to a specified probability of being a responder. The median serum concentration required for a 95% probability of being a responder is 27 µg/mL. An even more conservative approach is to use the upper bound (97.5th percentile) of the 95% probability of response corresponding to a serum concentration of 50 µg/mL.

Considering the simulated PK profiles of various doses as well as a period of at least 10 days within which it is considered relevant for the intended clinical setting to maintain serum

concentrations above the threshold level, the following doses (administered as a single IV infusion) are to be evaluated in Phase 1 of this study:

- Cohort 1 dose: 250 mg. This dose is expected to result in exposure above the median threshold value 27 µg/mL for 7 days.
- Cohort 2 dose: 500 mg. This dose is expected to result in exposure above the upper bound threshold value of 50 µg/mL for 7 days.
- Cohort 3 dose: 1000 mg. This dose is expected to result in exposure above the upper bound threshold value of 50 µg/mL for 21 days.

#### **4.4 End of Study Definition**

A subject is considered to have completed the study if he/she has completed all phases of the study, including the EOS visit.

The end of the study is defined as the date of the last visit of the last subject in the study.

## 5 Study Population

Prospective approval of protocol deviations to recruitment and enrolment criteria, also known as protocol waivers or exemptions, is not permitted.

The study population will include adult male and female subjects who tested positive for SARS-CoV-2 by RT-PCR or antigen test and who require medical care for COVID-19 in hospital setting (i.e., level 4 or 5 of the 8-point ordinal scale), but do not require non-invasive mechanical ventilation (includes for example high flow oxygen therapy, positive pressure ventilation), invasive mechanical ventilation or intensive care treatment.

### 5.1 Inclusion Criteria

Subjects are eligible to be included in the study only if all of the following criteria apply:

#### Demography

1. Is  $\geq 18$  years of age inclusive, at the time of signing the informed consent.
2. Is male or female

#### Type of Subject and Disease Characteristics

3. Has ongoing SARS-CoV-2 infection confirmed by positive RT-PCR test and/or positive antigen test  $\leq 72$  hours of randomisation\*. If the positive test result is older than 72 hours, a positive re-test (RT-PCR or antigen) during screening is required.
4. If dyspnoea and/or tachypnoea are present, an onset of at most 3 days prior to randomisation\* is allowed.
5. Requires medical care in hospital for COVID-19 (i.e., level 4 or 5 of the 8-point ordinal scale).

*\*For Part 1 randomisation means IWRS treatment registration.*

#### Contraception

Contraceptive use by men or women should be consistent with local regulations regarding the methods of contraception for those participating in clinical studies.

#### Male Subjects:

6. A male subject must agree to use contraception as detailed in Appendix 5 of this protocol during the treatment period and for at least 90 days after the last dose of study treatment.

Female Subjects:

7. A female subject is eligible to participate if she is not pregnant (see Appendix 5), not breastfeeding, and at least one of the following conditions applies:

- Not a woman of childbearing potential (WOCBP) as defined in Appendix 5.

OR

- A WOCBP who agrees to follow the contraceptive guidance in Appendix 5 during the treatment period and for at least 90 days after the last dose of study treatment.

**Informed Consent**

8. Is able and willing to give written informed consent for the study, or if due to COVID-19 restrictions written consent is not possible, verbal informed consent in the presence of an impartial witness will be obtained and documented in the medical record.

**5.2 Exclusion Criteria**

Subjects are excluded from the study if any of the following criteria apply:

**Medical Conditions**

1. Has a resting respiratory rate  $\geq 30$  per minute without oxygen supplementation.
2. Has severe or critical COVID-19 requiring non-invasive (e.g. high flow oxygen therapy) or invasive mechanical ventilation and/or intensive care treatment.
3. Has ongoing clinically significant thromboembolic event or coagulopathy, according to clinical, laboratory and/or radiological assessment.
4. Has a neutrophil to lymphocyte ratio  $> 4$ .
5. Has alanine aminotransferase (ALT) level  $> 5 \times$  upper limit of normal (ULN) or an aspartate aminotransferase (AST) level  $> 5 \times$  ULN. Known severe liver disease such as cirrhosis with Child-Pugh Class B or C.
6. Has renal impairment with estimated creatinine clearance  $< 30$  mL/min/1.73 m^2, or is receiving continuous renal replacement therapy, haemodialysis.
7. Has any other medical condition, which in the opinion of the Investigator, would impact the safety of the subject or interfere with the subject's ability to comply with the study and follow-up procedures.

8. Has active malignancy for which cytotoxic or cytostatic treatment is being administered or has been administered less than 3 months prior to enrolment, or which is in (pre-)terminal stage.
9. Has active chronic hepatitis B or C.

#### **Prior/Concomitant Therapy**

10. Has received any of the following therapies:
  - a. Any SARS-CoV-2 human intravenous immunoglobulin (hIVIG), convalescent plasma (convalescent plasma therapy) from a person who recovered from SARS-CoV-2 infection within 30 days prior to the study treatment administration.
  - b. Any other investigational or authorised biological medical product with a SARS-CoV-2 neutralising activity including but not limited to any monoclonal antibody within 30 days prior to the study treatment administration.
11. Has received an investigational or approved vaccination against SARS-CoV-2 within 14 days before study treatment start for the first vaccination dose and 7 days for subsequent vaccination doses, including 'booster shots'.

#### **Other Exclusions**

12. Has known allergy or hypersensitivity reaction to any monoclonal antibody or to any components of study treatment.
13. For WOCBP:
  - a. Pregnancy or a positive urine pregnancy test (within 72 hours prior to treatment). If the urine test is positive or cannot be confirmed as negative, a serum pregnancy test is required, and the subject will be excluded if the serum pregnancy test is positive.
  - b. Breastfeeding.

#### **Exclusion Criteria only Applicable to Part 1**

14. Has received or is receiving concomitant treatment with medicinal products with potential or demonstrated anti-SARS-CoV-2 (antiviral) activity, including but not limited to remdesivir, within 30 days prior to the study treatment administration.
15. Has renal impairment with estimated creatinine clearance  $< 60 \text{ mL/min/1.73 m}^2$ .

16. Has morbid obesity (body mass index  $> 35 \text{ kg/m}^2$ ), uncontrolled diabetes, cardiac insufficiency, uncontrolled high blood pressure, or any clinically significant (in the opinion of the Investigator) hepatic, pulmonary, gastrointestinal, genitourinary, endocrine, immunologic, metabolic, neurologic, or haematological disease.

### **5.3 Lifestyle Considerations**

No lifestyle restrictions are required.

### **5.4 Screen Failures**

Screen failures are defined as subjects who consent to participate in the clinical study but are not subsequently entered in a cohort (Part 1) or randomly assigned to study intervention (Part 2). A minimal set of screen failure information is required to ensure transparent reporting of screen failure subjects to meet the Consolidated Standards of Reporting Trials (CONSORT) publishing requirements and to respond to queries from regulatory authorities. Minimal information includes demography, reason for screen failure (e.g., eligibility requirements failed), and any SAEs.

Individuals who do not meet the criteria for participation in this study (screen failure) may not be rescreened.

#### **5.4.1 Screening and Enrolment Log and Subject Identification Numbers**

The subject's enrolment will be recorded in the Screening and Enrolment Log.

Upon enrolment, each subject will receive a unique subject identification number.

## 6 Study Treatment

Study treatment is defined as any investigational treatment(s), marketed product(s), or placebo intended to be administered to a study subject according to the study protocol.

XVR011 is for intravenous infusion only. It must not be administered as an intravenous push or bolus injection. Emergency resuscitative treatments, such as antihistamines, corticosteroids, bronchodilators, vasopressors must be available within the treatment area.

### 6.1 Study Treatments Administered

**Table 6–1 Study Treatments Administered**

| Arm/ Cohort Name:        | XVR011 Dose level 1                                                                                                                     | XVR011 Dose level 2 | XVR011 Dose level 3 | Placebo                                                                 |
|---------------------------------|------------------------------------------------------------------------------------------------------------------------------------------------|----------------------------|----------------------------|--------------------------------------------------------------------------------|
| Study Treatment Name:    | XVR011                                                                                                                                         |                            |                            | Placebo                                                                        |
| Type:                    | Biologics                                                                                                                                      |                            |                            | -                                                                              |
| Dosage Formulation:      | Solution for infusion                                                                                                                          |                            |                            | -                                                                              |
| Unit Dose Strength(s):   | 50 mg/mL (500 mg of XVR011 in 10 mL)                                                                                                           |                            |                            | -                                                                              |
| Dosage Level(s):         | 250 mg                                                                                                                                         | 500 mg                     | 1000 mg                    | Placebo                                                                        |
| Route of Administration: | IV infusion                                                                                                                                    |                            |                            |                                                                                |
| Use:                     | Experimental                                                                                                                                   |                            |                            | Placebo-comparator                                                             |
| IMP and NIMP:            | IMP                                                                                                                                            | IMP                        | IMP                        | NIMP                                                                           |
| Sourcing:                | XVR011 provided centrally by the Sponsor.
0.9% sodium chloride IV bag and accessories provided centrally by the Sponsor.                    |                            |                            | 0.9% sodium chloride IV bag and accessories provided centrally by the Sponsor. |
| Dosing Instructions:     | Study treatment diluted in 0.9% sodium chloride sterile solution for IV infusion to a concentration of 10 mg/mL (see Section 6.2 for details). |                            |                            |                                                                                |

|                                 |                                                                                                                                                                                                                                                 |  |                                              |
|---------------------------------|-------------------------------------------------------------------------------------------------------------------------------------------------------------------------------------------------------------------------------------------------|--|----------------------------------------------|
| Packaging and Labelling: | Study treatment will be provided in 20 mL neutral type I glass Schott vials (filled with 10 mL extractable volume). Each vial will be labelled per country requirement. Commercially available IV bags will be used for the dilution of XVR011. |  | Commercially available IV bags will be used. |
|---------------------------------|-------------------------------------------------------------------------------------------------------------------------------------------------------------------------------------------------------------------------------------------------|--|----------------------------------------------|

Abbreviations: IV = intravenous; IMP = investigational medicinal product; NIMP = non-investigational medicinal product.

The single dose treatment will be administered by a health care professional as an IV infusion (Table 6–2). The subject will be closely monitored by a health care professional during the IV infusion and for at least 120 minutes afterward. Sentinel subjects in Part 1 should be monitored for 24 hours after the infusion. Prior to the infusion, the subject should be informed of possible signs/symptoms of hypersensitivity and advised to immediately report if any of these occur.

The concentration of the prepared study treatment infusion is 10 mg/mL.

**Table 6–2 IV Infusion Details for Part 1**

| Dose                   | IV infusion volume | IV infusion rate                | IV infusion time |
|------------------------|--------------------|---------------------------------|------------------|
| 250 mg (Dose Level 1)  | 25 mL              | 1.0 mL/minute
(10 mg/minute) | 25 minutes       |
| 500 mg (Dose Level 2)  | 50 mL              |                                 | 50 minutes       |
| 1000 mg (Dose Level 3) | 100 mL             |                                 | 100 minutes      |

Abbreviation: IV = intravenous.

For Part 2, one dose will be selected from the 3 doses evaluated in Part 1, with the corresponding IV infusion volume.

The study treatment will be administered as an infusion using a sterile, non-pyrogenic, low-protein binding 0.2 µm in-line or add-on filter. After administration, the line should be flushed with 0.9% sodium chloride sterile solution for injection.

It will be documented if the full volume of the study treatment infusion was administered. If not the full volume, e.g. in case of interruption due to an infusion related reaction, then an approximation of the infused volume must be made and documented.

Infusion reactions: as with any protein, infusion reactions/hypersensitivity reactions may occur. This may vary from mild to moderate signs and symptoms but may also be a severe or life-threatening anaphylactic/anaphylactoid reaction. Signs and symptoms may include hypotension, tachycardia, bronchospasm, dyspnoea, oedema/angio-oedema, dizziness, headache, nausea, abdominal pain, fever, rash.

Guidance in case of an infusion reaction based on severity of the reaction is summarised in Table 6–3.

**Table 6–3                      Guidance in Case of an Infusion Reaction Based on Severity Of The Reaction**

| Infusion reaction   | Study treatment actions                                                                                                                                                                                                                                                    | Other treatment (see also institutional standard practice for infusion reactions)                                                             |
|----------------------------|-----------------------------------------------------------------------------------------------------------------------------------------------------------------------------------------------------------------------------------------------------------------------------------|------------------------------------------------------------------------------------------------------------------------------------------------------|
| Grade 1 - mild             | Reduce rate of infusion                                                                                                                                                                                                                                                           | Consider symptomatic treatment                                                                                                                       |
| Grade 2 - moderate         | Interrupt infusion
Restart infusion if signs/symptoms have responded well to symptomatic treatment
Infusion should be restarted at a slower rate:
If symptoms worsen or recur, permanently stop infusion
If symptoms do not worsen or do not recur, continue infusion | Administer symptomatic treatment e.g. antihistamines, NSAIDs wait for signs/symptoms to improve before re-starting infusion                          |
| Grade 3 - severe           | Permanently stop infusion                                                                                                                                                                                                                                                         | Administer antihistamines, corticosteroids, bronchodilators, IV fluids, vasopressors and other treatments as per Investigator judgement              |
| Grade 4 – life-threatening | Permanently stop infusion                                                                                                                                                                                                                                                         | Administer antihistamines, corticosteroids, bronchodilators, IV fluids, vasopressors and other life support treatments as per Investigator judgement |

Abbreviation: NSAID = nonsteroidal anti-inflammatory drugs

## 6.2 Preparation, Handling, Storage, and Accountability

The dose will be administered using an IV bag containing 0.9% (w/v) sodium chloride sterile solution, for an infusion concentration of 10 mg/mL, and delivered through an IV administration set with a sterile, non-pyrogenic, low-protein binding 0.2 µm in-line or add-on filter.

For Part 1, the study treatment is open-label XVR011 and the study treatment infusion bag is prepared at the hospital (central) pharmacy in controlled and aseptic conditions according to the instructions in the investigational medicinal product (IMP) handling instructions.

For Part 2, study treatment is blinded and is either XVR011 or placebo and is prepared at the hospital (central) pharmacy in controlled and aseptic conditions by an unblinded pharmacist as a covered IV infusion bag according to the instructions in the IMP handling instructions.

For placebo treatment, the covered IV bag with only 0.9% sodium chloride solution will be used.

The pharmacist or designee must maintain a log to confirm appropriate temperature conditions have been maintained during transit for all study treatment received, and any discrepancies are reported and resolved before the use of the study treatment.

The IV bags of study treatment (both XVR011 and placebo) will be covered to mask the slight colour difference between the XVR011 solution and placebo to maintain the study blind.

The study treatment infusion bag/cover will be identified with a sticker specifying the protocol number, subject ID number, date and time of preparation. The study treatment infusion must be administered as soon as possible after preparation and no later than 2 hours of the date and time of preparation noted on the bag/cover.

Only subjects enrolled in the study may receive study treatment and only authorised site staff may supply or administer study treatment. All study treatments must be stored in a secure, environmentally controlled, and monitored (manual or automated) area in accordance with the labelled storage conditions with access limited to the Investigator and authorised site staff.

The Investigator, institution, or the head of the medical institution (where applicable) is responsible for study treatment accountability, reconciliation, and record maintenance (e.g., receipt, reconciliation, and final disposition records).

Regarding storage, XVR011 will be provided as a single use vial with one vial per package. The vial must be stored in the package in which it is provided. The package should be stored at -20°C at the central pharmacy. For further details on storage, see the IMP handling instructions.

Vials will be prepared at the central pharmacy and may be discarded after use after accountability check. For details on IMP accountability, see the IMP handling instructions.

Further guidance and information for the final disposition of unused study treatment are provided in the IMP handling instructions.

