- **Endpoint assessment period (Day 2 to Day 29):** Subjects will remain hospitalised until at least 24 hours after study treatment administration. Hospital discharge after this period is at the discretion of the Investigator and will be based on the clinical condition of the subject. Study assessments will be performed every day up to Day 4 and then weekly until Day 29. Subjects who are discharged from the hospital before the Day 29 visit will return to the study site for each study visit until Day 29 (see Section 6.7 for details). Day 29 is considered as the EOS for part 1.
- **Extended follow-up period (Day 30 to Day 90) for part 2 only:** Subjects will return to the study site for 2 additional visits, on day 60 and day 90. Day 90 is considered as the EOS for part 2.

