### **6.3.2 Part 2**

#### **6.3.2.1 Randomisation and Blinding**

Part 2 is a randomised double-blind study.

All subjects will be randomised centrally using an interactive response technology (IRT) to ensure that treatment assignment is unbiased and concealed from study subjects and the Investigator. The Investigator will be provided with usernames and passwords for randomisation purposes and to unblind the study treatment in case of emergency, where he/she considers it essential to know what treatment the subject was taking. The IRT will be designed to send a confirmation (by fax and/or notification email) to the site for every transaction performed by the Investigator.

Each subject will be assigned to one of the 2 arms of the study according to the randomisation schedule provided by the Parexel Informatic Manager utilising a validated computer program. Details of the procedure are described in the IRT Manual provided to all sites.

Subjects will be randomly assigned in a 2:1 ratio to receive study treatment (XVR011 or placebo). Stratification will be done at randomisation for country and for fully vaccinated/prior SARS-CoV-2 infection. Any EMA approved, FDA approved or WHO recommended vaccine will be taken into account. The original recommended vaccination frequency (either 1 or 2 injections depending on the vaccine) will be considered as fully vaccinated, i.e. the more recent recommendations for a booster shot are not required for the stratification definition.

The placebo IV bag will present the same external appearance with the same composition, except for the active ingredient. IV bag cover will be added to keep the blinding on the IV bag.

Randomisation data will be kept strictly confidential, accessible only to authorised persons, until the time of unblinding of the allocated treatment of all study subjects after locking the database upon termination of the study.

Subjects, Investigators and/or employees of the investigational site will remain blinded to each subject's assigned study treatment throughout the course of the study, unless in case of emergency.

In order to maintain this blind, an otherwise uninvolved third party (unblinded pharmacist) will be responsible for the reconstitution and dispensation of all study treatment and will endeavour to ensure that there are no differences in time taken to dispense following randomisation.

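### Masking is specified for the IV bag only despite an acknowledged colour difference, so the infusion line may reveal the arm; the matched-composition sentence also needs reconciling with a saline-only placebo

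*Protocol*

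**What the plan says.** Protocol section 6.2 states that the bags in both arms "will be covered to mask the slight colour difference between the XVR011 solution and placebo to maintain the study blind". Section 6.3.2.1 repeats the measure with the same reach: "IV bag cover will be added to keep the blinding on the IV bag". In Part 2 the infusion is prepared "by an unblinded pharmacist as a covered IV infusion bag according to the instructions in the IMP handling instructions".

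From the bag, the dose is "delivered through an IV administration set with a sterile, non-pyrogenic, low-protein binding 0.2 µm in-line or add-on filter". Table 6–2 gives 25, 50 or 100 minutes depending on the dose level, and Part 2 uses one of these levels. Section 6.1 adds: "After administration, the line should be flushed with 0.9% sodium chloride sterile solution for injection". No cover, sleeve or tinted set is mentioned for any part of the line.

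On what is in the bags, section 6.3.2.1 says: "The placebo IV bag will present the same external appearance with the same composition, except for the active ingredient". Section 6.2 says: "For placebo treatment, the covered IV bag with only 0.9% sodium chloride solution will be used".

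On the people involved, section 6.4 has the Investigator or a designee give the treatment. Section 6.1 has a health care professional watch closely during the infusion and for at least 120 minutes after it. The unblinded pharmacist's role in section 6.3.2.1 is limited to reconstituting and dispensing. Subjects, Investigators and site staff are meant to stay blinded.

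**The concern.** The sponsor judged the colour difference large enough to threaten the blind, and then masked only the container. The same fluid passes through the line in front of people who must remain blinded. If the tint can be seen there, the saline flush adds a second cue: with XVR011, clear fluid follows whatever colour is left in the tubing, while with placebo nothing changes.

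This matters because recovery is partly a judgement. In Appendix 2, for a hospitalised subject off oxygen, levels 4 and 3 differ only in whether ongoing medical care is needed. Levels 1 and 2 require discharge, and section 4.1 says: "Hospital discharge after this period is at the discretion of the Investigator and will be based on the clinical condition of the subject". Symptom ratings come from the subject, and the Investigator judges whether an adverse event is related. Knowledge of the arm could move all of these in one direction, and the analysis cannot repair a blind once it is lost.

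The composition sentence is a smaller matter. A reader of section 6.3.2.1 would expect a vehicle-matched placebo, and section 6.2 describes plain saline.

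**Working it through.** **Step 1: how far the masking reaches.** The text can be followed along the fluid path.

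| Element | Masking stated in the protocol |
|---|---|
| Bag | Covered in both arms (6.2, 6.3.2.1) |
| Drip chamber, tubing, filter | Not addressed |
| Post-infusion flush | Not addressed |

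**Step 2: who is at the line.** The Investigator or designee gives the infusion (6.4) and a health care professional watches it (6.1). Section 8.1.1 does not say who scores the 8-point scale. The Investigator decides discharge (4.1). No passage requires the scorer, or the person deciding discharge, to be someone who was not at the infusion.

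**Step 3: composition.** Inputs are the vial strength of 50 mg/mL (Table 6–1) and the infusion concentration of 10 mg/mL (6.1, 6.2).

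Share of vial solution in the active infusion = 10 / 50 = 20%, that is 5 of 25 mL, 10 of 50 mL or 20 of 100 mL. In the placebo infusion the share is 0%.

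The two composition sentences agree only if the vial holds nothing but XVR011 in 0.9% sodium chloride. The protocol does not list the vial's other contents, so the matched-composition statement is unsupported as it stands.

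**Step 4: what a visible arm could do to the test.** The protocol gives no figure to reproduce here. The scenario assumes:

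- no true effect, with both arms on the placebo curve of Table 9–1 (100%, 80%, 50% and 20% unrecovered at Days 1, 5, 7 and 29);
- 272 against 136 subjects, 15% drop-out, and a whole-day log-rank test at one-sided 2.5%;
- a chosen share of XVR011 subjects scored recovered earlier, always in the favourable direction.

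The table gives the range over three separate runs of 3,000 trials per scenario.

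| XVR011 subjects affected | Shift | False-positive rate |
|---|---|---|
| 0% | none | 2.0% to 2.4% |
| 25% | 1 day | 3.2% to 4.3% |
| 50% | 1 day | 5.7% to 6.4% |
| 100% | 1 day | 11.4% to 12.3% |
| 25% | 2 days | 5.0% to 5.7% |

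With 5% to 10% affected by one day, a single run gives about 2.9%. The simulation standard error near the nominal level is √(0.025 × 0.975 / 3000) ≈ 0.3 percentage points, so 2.9% cannot be told apart from 2.5%. The simulations ignore stratification and the 14-day sustained-recovery rule.

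**The case against.** The strongest reply is that unmasking is inferred. The protocol calls the difference slight and does not say whether it can be seen in narrow tubing at 10 mg/mL. Each subject receives one infusion, so nobody has a side-by-side comparison for that subject. Sections 6.2 and 6.3.2.1 may not be the whole story either: the IMP handling instructions are not shown, and the sponsor supplies the accessories centrally (Table 6–1), so line covers may already be required. All of this stands. A reader might infer that the line does give the arm away; the documents support only that it may.

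The other safeguards are real: central allocation, an unblinded pharmacist outside the study team, effort to equalise dispensing times, a blinded sponsor, drug concentrations withheld from sites, and per-protocol exclusions decided before unblinding. None of them bears on what can be seen in the line.

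The endpoint also has some protection. Level 5 against level 4 turns on supplemental oxygen, and recovery must hold for 14 consecutive days, so a premature discharge followed by a relapse would not count. That limits the bias but does not remove it: a subject called recovered one day early who then stays well passes the 14-day rule.

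On composition, a reader might conclude that section 6.3.2.1 is false. The documents do not show that. No excipients are listed, the colour could come from the protein itself, and the cover can satisfy the statement about external appearance.

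**Conclusion.** The point holds as a gap in the masking and an inconsistency in the placebo description. The protocol admits a visual cue, covers it at the bag only, and does not keep the people who can see the line apart from those whose judgement feeds the primary endpoint. Following the bag-only rule as written leaves that cue unaddressed downstream.

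The size of any bias is unknown. The rates of about 4% to 12% are conditional on assumed shares and shifts that nothing in the protocol supplies. The upper end requires every XVR011 subject to be recognised and moved by a whole day, which is hard to believe for a slight tint; at 5% to 10% affected there is no detectable inflation. These figures show what kind of harm is possible and should not be read as an estimate for this trial.

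This is a low-cost improvement to make before Part 2 starts. It does not show that the blind will fail.

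**What to change.** In sections 6.2 and 6.3.2.1, require opaque sleeves or tinted sets over the full fluid path (drip chamber, tubing and filter) in both arms, left in place until the post-infusion flush is complete. Align the IMP handling instructions if they do not already require this.

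Replace the composition sentence in section 6.3.2.1 with one that agrees with section 6.2, for example: *placebo is 0.9% sodium chloride in the same volume as the active infusion, and bag and line are covered in both arms.* It should say nothing about excipients, because the protocol lists none.

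The cost is sleeves or tinted sets added to the accessories the sponsor already supplies, and a short paragraph of wording. No extra staff are needed. The one downside is that a covered line is slightly harder to inspect during the infusion.
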